## Abstract

**Background:**

Catgut implantation at acupoints has been used in China to treat allergic rhinitis (AR) for a long time. However, its efficacy and safety in the treatment of AR is controversial due to the poor quality of the clinical trial of this therapy. This study aims to identify whether catgut implantation at acupoints is indeed an effective and safe treatment for patients with persistent or intermittent allergic rhinitis (PER or IAR) by comparing with sham catgut implantation treatment.

**Methods and design:**

This study compares real *versus* sham catgut implantation at acupoints in 242 patients with a history of PER or IAR and with a positive skin prick test (SPT). The trial will be conducted in the Teaching Hospital of Chengdu University of Traditional Chinese Medicine. In the study, patients will be randomly assigned by computer-generated randomization list into two groups and assessed prior to treatment. Then, they will receive two sessions of treatments (once per 2 weeks) for 4 consecutive weeks and have a follow-up phase of 12 weeks. The administration of catgut implantation (or sham-control) at acupoints follows the guidelines for clinical research on acupuncture (WHO Regional Publication, Western Pacific Series No.15, 1995), and is performed double-blindly by a well-trained physician in acupuncture. The main outcome measures include the primary and secondary indicators. Primary indicators are subjective symptoms scores evaluated by visual analogue scales (VAS) and Rhinoconjunctivitis Quality of Life Questionnaires (RQLQ). The secondary indicators are the results of laboratory examinations, such as serum allergen-specific IgE, nasal inflammatory cells counts (mast cells, eosinophils, and T cells) and nitric oxide concentration in nasal excretion. The use of anti-allergic medication will also be recorded as one of the secondary indicators. Furthermore, adverse events will be recorded and analyzed. If any participants withdraw from the trial, intention-to-treat analysis (ITT) and per-protocol (PP) analysis will be performed.

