## Methods and design

### Study design

This study will be a double-blind, randomized, sham-controlled trial conducted in the Department of Otorhinolaryngology-head and neck surgery, Teaching Hospital of Chengdu University of T.C.M., China. This study includes the following time points: a run-in period of 4 weeks after screening, a treatment period of 4 weeks, and a follow-up period of 12 weeks. The total study period will be 20 weeks. At the screening visit, medical history especially in relation to AR and other allergic diseases will be asked and recorded by a study physician based on a systemically designed questionnaire. Patients who satisfy the inclusion criteria will be recruited into the run-in period. After randomization, patients will be blindly assigned to either the real catgut implantation at the acupoints group or the sham group (controls). All patients will receive two treatments over a period of 4 weeks. Chlorphenyramine will be used as a rescue medication if the patients present with untolerable AR symptoms. At the same time, patients should complete visual analogue scales (VAS) [9] and Rhinoconjunctivitis Quality of Life Questionnaires (RQLQ) [10,11] before randomization, at the end of treatment, during and after the follow-up period, respectively. Meanwhile, inflammatory cells and mediators in nasal secretions will also be measured at these three visits. Outcome measurements will be assessed by evaluating the efficacy and safety of catgut implantation at acupoints in the treatment of AR.

The design of this study followed the guidelines of the Helsinki Declaration (Version Edinburgh 2000) and was approved by Sichuan Regional Ethics Review Committee on Traditional Chinese Medicine (TCM). Informed consent are to be obtained from all the study patients. Before signing the consent, all patients will be given enough time to decide whether to participate in the trial. Other treatment options instead of catgut implantation at acupoints will be available for those who are unwilling to be recruited in the study.

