### Randomization and blinding

Random number of allocation sequence will be generated by computer (using SPSS 15.0 statistical software package). A computer program that allows the patients to be assigned to either the real catgut implantation group or the sham-controlled group in a 1:1 ratio will be used. The random numbers will then be sealed in opaque envelopes. Participants who meet the inclusion criteria will be asked to pickup one of the envelopes. At the same time, the participants’ random numbers and the corresponding randomization information which includes the participant’s name in a pinyin format, the participant’s numerical birthday, and gender will be recorded in a random allocation table in duplicate and sealed in opaque envelopes, respectively. These opaque envelopes should be preserved separately by the principal investigator and the primary sponsor. The envelopes must be kept intact until cease blinding. The administrator who is in charge of random allocation should not participate in enrolling patients. Participants, researchers, and study physicians who interview and recruit patients are blinded to the group assignments. The acupuncturists are responsible for treatment proceedings of both groups, and therefore it would be difficult to blind the acupuncturists during the study. However, they will not communicate with the study patients nor participate in the assessment of study outcomes.

The two randomized groups will be named A or B in the medical records and case report forms which are not directly link to the treatment. All information will be lockedout and saved in a database before statistical analysis is performed. After statistical analysis, the blind exposure will be provided. The two opaque envelopes which contain the random allocation tables should be unsealed by the principal investigator and the primary sponsor simultaneously to clarify which group is the real treatment group or the sham-controlled group.

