#### Inclusion criteria

Patients who will be recruited in this study should meet the inclusion criteria including:

(1) aged between 18 and 70 years

(2) not be taking part in any other clinical trials

(3) having no previous experience of catgut implantation at acupoints

(4) provide written informed consent

(5) presenting with typical symptoms of AR, such as rhinorrhoa, sneezing, nasal obstruction, and pruritus. These symptoms should last >1 h on most days. Some patients may have ocular symptoms due to outdoor allergens

(6) with positive skin prick tests performed by trained health professionals

A standardized vaccine (Alutard SQ, ALK- Abelló, Denmark) will be used in the prick test. Oral H1-antihistamines are not permitted before skin test. Skin prick tests should be read at the peak of their reaction by measuring the wheal and the flare approximately 15 min after the performance of the test.

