### Statistical analysis

In our preliminary study to compare the efficacy of catgut implantation at acupoints with intranasal glucocorticoid, it was suggested that efficiency was 93.75% in the catgut implantation group and 96.88% in the control group. In this study, we anticipate an improvement of no less than 15% after real catgut implantation at acupoints. However, there are no previous data regarding the VAS or RQLQ scores for the treatment of AR with catgut implantation at acupoints. Considering participants recruited in the two groups are in a 1:1 ratio, the following formula was used to estimate sample size [13]:

$$n_{1}=n_{2}={\left[\frac{Z_{\alpha }\sqrt{2\pi_{c}\left(1-\pi_{c}\right)}+Z_{\beta }\sqrt{\pi_{1}\left(1-\pi_{1}\right)+\pi_{2}\left(1-\pi_{2}\right)}}{\pi_{1}-\pi_{2}}\right]}^{2}$$

In the formula: n1, n2 represents the sample size of each group. π1, π2 is the overall rate of each sample, respectively. πc = (π1 + π2)/2, α = 0.05, Z_0.05_ = 1,96,β = 0.10,Z_0.10_ = 1.282. Statistical analysis will be performed using a 5% significance and 90% power, resulting in an estimated 121 patients per group.

To test our hypothesis, the first step is to assess the baseline characteristics of two groups using an unpaired *t* test or *x*^2^ testes. The second step is to compare the efficacy of real catgut implantation with the sham one, including the primary and secondary outcomes using two-sample t test. If there is any case lost in follow-up phase or withdrawn from the trial, the causes of withdrawal should be clarified. The intention-to-treat analysis (ITT) and per-protocol (PP) analysis should be conducted to test whether the result of this trial is credible. For relief medication, within-group as well as between-group comparisons of scores are to be made. Data will be analyzed using the Statistical Package for the Social Sciences software, version 15.0 for Windows (SPSS Inc., Chicago, IL, USA). Data are presented as mean and 95% confidence intervals (CI). The statistical analysis will be performed in a blinded manner by qualified statisticians.

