### Trial status

The recruitment of patients started June 1,2012, and it is expected that by March 31, 2013 the required sample size will be reached.

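### Persistent and intermittent rhinitis are pooled, but disease type enters neither the stated randomization nor the stated t test, which gives up precision without biasing the comparison

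*Protocol article*

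**What the plan says.** The abstract's aim covers "patients with persistent or intermittent allergic rhinitis (PER or IAR) by comparing with sham catgut implantation treatment", and the trial enrols "242 patients with a history of PER or IAR and with a positive skin prick test (SPT". The inclusion criteria do not define the two types. On symptom duration they ask that "These symptoms should last >1 h on most days".

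Under Randomization and blinding, patients are "assigned to either the real catgut implantation group or the sham-controlled group in a 1:1 ratio will be used"; no stratification factor or block is stated. Trial status says that "The recruitment of patients started June 1,2012, and it is expected that by March 31, 2013 the required sample size will be reached", a span of ten months. Study design sets "a run-in period of 4 weeks after screening, a treatment period of 4 weeks, and a follow-up period of 12 weeks", so each patient is observed for 4 + 12 = 16 weeks of treatment and follow-up.

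Statistical analysis first compares baseline characteristics between the groups, then plans to "compare the efficacy of real catgut implantation with the sham one, including the primary and secondary outcomes using two-sample t test". Study design also has a physician take the AR history at screening with a structured questionnaire, so the information needed to classify type should already be collected.

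**The concern.** The aim names two disease types whose labels imply different persistence of symptoms. If VAS or RQLQ levels differ between them, the difference becomes part of the residual variance of a two-sample t test, because that test has no place for a covariate. The same applies to time of year, since patients enter over ten months. A listing without strata also lets the share of each type drift apart between arms by chance.

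At stake are the width of the confidence interval and the power of the main comparison, and how far a reader can trust that an observed difference is not partly a difference in case mix. The article names a specific test for the outcomes, so this concerns a stated method and is not merely a detail left to another document.

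**Working it through.** **The plan's own figure.** Statistical analysis gives 121 per group (two-sided 5%, 90% power). The two rates are not printed. With π1 = 0.9375 (the pilot catgut rate) and the 15% read as relative, π2 = 0.9375 × 0.85 = 0.7969 and πc = 0.8672. The printed formula gives [(0.9407 + 0.6019) / 0.1406]² = 120.3, so 121. The figure reproduces under that inferred reading. It is based on proportions and makes no reference to AR type.

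**Inputs for the check.** n = 121 per arm comes from the article. The article gives no IAR share q, no VAS SD and no PER-IAR difference d. Assumed: q = 20% to 50%, within-type SD 2.5 cm (variance 6.25), d = 1, 2 or 3 cm.

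**Chance imbalance in IAR share under simple 1:1 allocation.** SD of the difference in shares = √[2q(1−q)/121].
- q = 20%: SD 0.0514, 95% range ±10.1 points; a gap above 10 points in about 5% of trials.
- q = 30%: SD 0.0589, ±11.5 points; about 9%.
- q = 50%: SD 0.0643, ±12.6 points; about 12%.

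**Variance removed by adjusting for type.** Between-type variance = q(1−q)d². Share of the total = q(1−q)d² / [6.25 + q(1−q)d²]. Equivalent gain in patients = q(1−q)d² / 6.25. The 95% margin of the unadjusted difference = 1.96 × √(2 × total variance / 121).

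| q | d (cm) | Between-type variance | Share removed | Equivalent extra patients | Unadjusted margin (cm) |
|---|---|---|---|---|---|
| 20% | 1 | 0.16 | 2.5% | 2.6% | ±0.64 |
| 20% | 2 | 0.64 | 9.3% | 10.2% | ±0.66 |
| 20% | 3 | 1.44 | 18.7% | 23.0% | ±0.70 |
| 50% | 1 | 0.25 | 3.8% | 4.0% | ±0.64 |
| 50% | 2 | 1.00 | 13.8% | 16.0% | ±0.68 |
| 50% | 3 | 2.25 | 26.5% | 36.0% | ±0.73 |

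With type in the model the margin is about 1.96 × √(2 × 6.25 / 121) = ±0.63 cm in every row.

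**Imbalance and lost variance are one quantity.** At q = 50% and d = 2, the variance that imbalance adds to the treatment difference is (2 × 0.0643)² = 0.0165. The between-type part of the t test's squared standard error is 1.00 × 2/121 = 0.0165. The two must not be added: the risk of imbalance is already inside the unadjusted confidence interval. Adjustment narrows that interval; it does not repair an invalid one.

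**The case against.** The strongest reply is that nothing is wrong with the comparison. Enrolling both types is a legitimate broad-population choice. Concurrent 1:1 allocation balances type and month of entry in expectation, the sham arm has the same expected natural course, and a baseline comparison is planned. All of this stands, and it is why the point concerns efficiency. The baseline comparison may reveal an imbalance but does not change the t test that follows.

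A reader might go further and infer that spontaneous remission of intermittent patients over the 16 weeks distorts the durability comparison. The article does not support that. Its acupoint rationale mentions a remission stage and recurrence of AR in general, but it nowhere describes the course of either type or of seasonal exposure. The mention of outdoor allergens in the inclusion criteria concerns eye symptoms in some patients, and the criterion on symptom duration may limit how many intermittent patients enter. Equal remission in both arms could dilute a late contrast, but it could not favour one arm. Nor does the article support resting the durability conclusion on PER patients alone: that would set aside part of the population named in the aim, and durability is not designated as the primary comparison.

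It is also fair to say that the article condenses a fuller protocol, so strata or adjusted analyses may be written elsewhere. The point therefore extends only to the allocation and the test as described here.

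**Conclusion.** The point holds as a matter of precision. AR type is part of the stated population but of neither the stated allocation nor the stated test. There is no systematic bias.

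On the assumed SD and differences, adjustment is worth between 2.5% and 26% of the variance. A 50% IAR share is the worst case for both imbalance and variance, and at 20% the gain is at most about 19%. If PER and IAR patients hardly differ on VAS, the gain is negligible. No figure is offered for calendar period or for RQLQ, because the article gives nothing from which to derive one. The change is worth making because it improves a named method at almost no cost.

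**What to change.** 1. Define PER and IAR and classify every patient at baseline from the screening history.
2. For patients still to be randomized, stratify the allocation list by type, in permuted blocks. Envelopes must then be taken in sequence within each stratum; the present text has participants pick one up, and a free choice would defeat the blocks.
3. For VAS and RQLQ, replace the two-sample t test with a linear model containing treatment, AR type and calendar period of randomization, specified before unblinding. This can cover all 242 patients, including those already enrolled.
4. Keep the pooled adjusted treatment estimate as the main result, and report PER and IAR estimates as supportive.

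The cost is one stratification factor, two model terms, and subgroup estimates that are less precise than the pooled one. Recruitment has begun, so stratification can reach only later patients. None of these steps restores a treatment contrast that is diluted because IAR patients remit equally in both arms; the separate estimates would only help to show it.

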**Discussion:**

The important features of this trial include the randomization procedures, large sample, and a standardized protocol of catgut implantation at acupoints. This trial will be the first study with a high evidence level in China in order to assess the efficacy and safety of catgut implantation at acupoints in treatment of AR following a randomized, double-blind sham-controlled method.

**Trial registration:**

Chinese Clinical Trial Registry: ChiCTR-TRC-12002191

## Background

Allergic rhinitis (AR) is an IgE-mediated immune disease triggered by allergens with symptoms of nasal obstruction, itching, watery rhinorrhea, and sneezing. AR has become a major health problem worldwide. It has been estimated by the ARIA (Allergic Rhinitis and its Impact on Asthma) 2008 document that over 600 million patients from all countries, in all ethnic groups, and of all ages suffer from AR [1]. In China, the prevalence of allergic rhinitis has increased to 24.6% in 2007 according to the epidemiological study in 11 major cities in China [2]. Furthermore, there is a well-documented relationship existing between nasal allergy and asthma. The prevalence of asthma in patients with rhinitis could reach up to 40%, and the majority of patients with asthma experience rhinitis symptoms [1].

AR causes an impairment on the quality of life (QOL) of patients and results in significant healthcare costs. As an available and affordable treatment choice, acupuncture has been accepted as a therapeutic option for relieving symptoms of AR in China and other countries [3-7]. Catgut implantation at acupoints is a subtype of acupuncture, which can be embedded in the acupoint by using a special needle. A period of time may be needed for the catgut to be completely absorbed by the tissue. Therapeutic effects can be achieved by continuing stimulation caused by the catgut at the acupoint. Therefore, catgut implantation at acupoint may be effective in treating some chronic disease such as AR.

Although catgut implantation at acupoint has been used in treating diseases for a few thousand years in China, there have been very few clinical trials which have been strictly designed to verify the efficacy and safety of this treatment for AR [8]. It is indeed necessary to obtain high level of evidences for catgut implantation at acupoints in the treatment of AR (Figure 1).

**Figure 1 F1:**
[figure not shown]
**Trial flowchart ****(*****blindly assessed****).**

We have recently conducted a pilot clinical trial to compare the efficiency of catgut implantation at acupoint with triamcinnone acetonide nasal spray in the treatment of AR. The results suggested that therapeutic efficacies were similar between these two groups at the end of the 4-week period of treatment. However, after 3 months of follow-up, the recurrence rate of AR was much lower in the catgut implantation group than in the intranasal glucocorticoid one. Furthermore, symptom-free days were longer in the catgut implantation group.

Based on this pilot study, we wish to design a randomized, double-blind, large-scale clinical trial to compare the effectiveness and safety of real catgut implantation at acupoints with those of the sham one for AR. The design and methodologies of this study has been approved by Sichuan Regional Ethics Review Committee on Traditional Chinese Medicine with an ethics approval number of 2012KL-002. The work reported in this article is registered with an identifier (ChiCTR-TRC-12002191) by Chinese Clinical Trial Registry.

## Methods and design

### Study design

This study will be a double-blind, randomized, sham-controlled trial conducted in the Department of Otorhinolaryngology-head and neck surgery, Teaching Hospital of Chengdu University of T.C.M., China. This study includes the following time points: a run-in period of 4 weeks after screening, a treatment period of 4 weeks, and a follow-up period of 12 weeks. The total study period will be 20 weeks. At the screening visit, medical history especially in relation to AR and other allergic diseases will be asked and recorded by a study physician based on a systemically designed questionnaire. Patients who satisfy the inclusion criteria will be recruited into the run-in period. After randomization, patients will be blindly assigned to either the real catgut implantation at the acupoints group or the sham group (controls). All patients will receive two treatments over a period of 4 weeks. Chlorphenyramine will be used as a rescue medication if the patients present with untolerable AR symptoms. At the same time, patients should complete visual analogue scales (VAS) [9] and Rhinoconjunctivitis Quality of Life Questionnaires (RQLQ) [10,11] before randomization, at the end of treatment, during and after the follow-up period, respectively. Meanwhile, inflammatory cells and mediators in nasal secretions will also be measured at these three visits. Outcome measurements will be assessed by evaluating the efficacy and safety of catgut implantation at acupoints in the treatment of AR.

The design of this study followed the guidelines of the Helsinki Declaration (Version Edinburgh 2000) and was approved by Sichuan Regional Ethics Review Committee on Traditional Chinese Medicine (TCM). Informed consent are to be obtained from all the study patients. Before signing the consent, all patients will be given enough time to decide whether to participate in the trial. Other treatment options instead of catgut implantation at acupoints will be available for those who are unwilling to be recruited in the study.

### Randomization and blinding

Random number of allocation sequence will be generated by computer (using SPSS 15.0 statistical software package). A computer program that allows the patients to be assigned to either the real catgut implantation group or the sham-controlled group in a 1:1 ratio will be used. The random numbers will then be sealed in opaque envelopes. Participants who meet the inclusion criteria will be asked to pickup one of the envelopes. At the same time, the participants’ random numbers and the corresponding randomization information which includes the participant’s name in a pinyin format, the participant’s numerical birthday, and gender will be recorded in a random allocation table in duplicate and sealed in opaque envelopes, respectively. These opaque envelopes should be preserved separately by the principal investigator and the primary sponsor. The envelopes must be kept intact until cease blinding. The administrator who is in charge of random allocation should not participate in enrolling patients. Participants, researchers, and study physicians who interview and recruit patients are blinded to the group assignments. The acupuncturists are responsible for treatment proceedings of both groups, and therefore it would be difficult to blind the acupuncturists during the study. However, they will not communicate with the study patients nor participate in the assessment of study outcomes.

The two randomized groups will be named A or B in the medical records and case report forms which are not directly link to the treatment. All information will be lockedout and saved in a database before statistical analysis is performed. After statistical analysis, the blind exposure will be provided. The two opaque envelopes which contain the random allocation tables should be unsealed by the principal investigator and the primary sponsor simultaneously to clarify which group is the real treatment group or the sham-controlled group.

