### Recruitment

#### Hospital recruiting

In China, most of the patients with symptoms of AR will present at the otorhinolaryngology clinics. It is advisable that all physicians in our department should be familiar with the study inclusion and exclusion criteria and refer the appropriate patients to the PI or study physicians. Then the screening evaluations will be conducted and the information of the patients will be recorded. Patients who satisfy the inclusion criteria and are willing to participate in the trial will sign on the written informed consent. Then they will be randomized into either of the study groups and introduced to the acupuncturists.

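### Patients pick their own envelope, so adherence to the generated order cannot be checked; separately, the text conflicts on whether randomisation precedes or follows the 4-week run-in

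*Protocol article*

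**What the plan says.** All references are to the protocol article.

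**Issue of envelopes (Randomization and blinding).** The numbers come from software: "Random number of allocation sequence will be generated by computer (using SPSS 15.0 statistical software package". Allocation is to the "real catgut implantation group or the sham-controlled group in a 1:1 ratio will be used". Then: "The random numbers will then be sealed in opaque envelopes". The next step is "Participants who meet the inclusion criteria will be asked to pickup one of the envelopes". The section gives no numbering on the envelopes and no order of opening. Each participant's number and identifying details "will be recorded in a random allocation table in duplicate and sealed in opaque envelopes, respectively", with one copy held by the principal investigator and one by the sponsor. On roles: "The administrator who is in charge of random allocation should not participate in enrolling patients".

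**Timing.** Study design has a 4-week run-in after screening: "Patients who satisfy the inclusion criteria will be recruited into the run-in period". It mentions randomisation after that, and has VAS and RQLQ completed before randomisation. Hospital recruiting describes screening, eligibility and signed consent, and continues: "Then they will be randomized into either of the study groups and introduced to the acupuncturists". It does not mention a run-in.

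**The concern.** **Order of issue.** A generated list guards against selection most firmly when each new patient must take the next entry. The date of entry and the list position can then be compared, and any departure shows. If the patient picks from a pool, there is no expected next entry to compare with. Any blocking in the list would also be dissolved (the article mentions none). This matters more here because the trial is run in one department, the article concedes that the acupuncturists are difficult to blind, and Quality control has them trained in the randomisation method. The Abstract lists the randomisation procedures among the trial's important features.

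**Time point.** Whether randomisation comes before or after the run-in decides who belongs to the intention-to-treat set. A patient who leaves during a run-in that precedes randomisation was never in the trial comparison. One who leaves during a run-in that follows randomisation is a missing outcome in one of the arms.

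The two points are independent. The time of randomisation has no bearing on whether the list order is followed.

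**Working it through.** **1. What the pick loses and what it keeps**

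| Feature | Fixed by | Checkable afterwards? |
|---|---|---|
| Link from number to arm | computer list | yes |
| Which patient holds which number | the pick, then the duplicate table | yes, from the table |
| Order in which numbers were issued | the pick | no, there is no expected order |
| Envelope returned or swapped before recording | not covered | no |
| Envelope discarded | not covered | only if used and unused numbers are counted against the list; no such count is described |

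*Is the pick itself biased?* Assume a pool of 121 + 121 indistinguishable envelopes. The article states 1:1 and 121 per group but does not describe the pool. If all 242 are used, the final split is exactly 121:121. After 121 draws, let X be the number assigned to arm A. The difference between arms is 2X − 121, and X is hypergeometric, so

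SD = 2 × √(121 × ½ × ½ × 121/241) = 2 × √15.19 ≈ 7.8 patients.

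A blind draw thus gives ordinary chance imbalance on the way and the planned ratio at the end. It does not favour either arm.

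**2. The time point, section by section**

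| Section | What it implies |
|---|---|
| Study design | inclusion, 4-week run-in, then randomisation; VAS and RQLQ before randomisation |
| Randomization and blinding | the pick is tied to meeting the inclusion criteria; no date |
| Hospital recruiting | screening, consent, randomisation, acupuncturists; no run-in |
| Abstract (Methods and design) | assignment is listed before the pre-treatment assessment |
| Secondary outcome | diaries at baseline, then every 2 weeks after randomisation |
| Patient safety | screening laboratory tests before randomisation |

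The RQLQ schedule in Primary outcome is a further check: every 4 weeks, five times in total.

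- Counted from the start of treatment: (4 + 12)/4 + 1 = 5 (weeks 0, 4, 8, 12, 16).
- Counted from the start of the run-in: (4 + 4 + 12)/4 + 1 = 6.

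Five assessments fit a baseline at the end of the run-in. Since Study design puts these scores before randomisation, the schedule agrees with randomisation after the run-in. Hospital recruiting is the section that plainly departs from this. Randomization and blinding is open to either reading, because it uses the same trigger (meeting the inclusion criteria) that Study design uses for entry to the run-in.

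**3. Room for run-in losses.** Statistical analysis gives 121 per group as the result of its formula, and the Abstract gives 242 in total. As 2 × 121 = 242, no allowance for losses is shown on top of the formula's result. The article gives no expected run-in loss, so its effect cannot be sized.

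**The case against.** **The computer still governs allocation.** A reader might infer that picking makes the computer list irrelevant and the allocation unauditable. The documents do not support that. The envelopes hold computer-generated numbers, the arm for each number is preset, and the duplicate table shows who received which number. This stands: what is lost is the order and the check on it.

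**No route to bias is shown.** Steering needs someone who knows an envelope's contents and can influence the pick. Participants, researchers and recruiting physicians are blinded, the allocation administrator does not enrol, and patients meet the acupuncturists only after randomisation. The acupuncturists' training in the randomisation method gives them no part in enrolment. This also stands, and it is why no bias is asserted. A reader might still try a figure: 6 of 121 patients per arm steered and a 1 SD difference in prognosis. That gives 2 × 6/121 × 1 ≈ 0.10 SD if each steered patient lies 1 SD from average, or 2 × 6/121 × 0.5 ≈ 0.05 SD if the two steered groups lie 1 SD apart. Both inputs are invented, so neither result says anything about this trial.

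**The article is condensed.** Numbering and logs may be in the full protocol, and the wording could loosely describe a patient being handed the next envelope. This stands only in part. Silence on numbering would be no finding, but having the patient pick is a stated step, and its plain reading is a choice among envelopes.

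**The timing conflict is one loose section.** Most of the text favours randomisation after the run-in, and the trial flowchart, not available to this review, may settle it. A reader might also infer that baseline scores are taken after allocation, but Study design says the opposite. What remains is that Hospital recruiting, which describes how patients are brought in, gives a different sequence.

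**Conclusion.** Both points hold in limited form.

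1. As described, the pick and not the generated order decides which number each patient receives. For none of the 242 planned assignments could adherence to the list order be verified, and a repeated or swapped pick before recording would not show. This is a weakness in concealment and auditability, not a demonstrated bias, and no bias size can be given from the documents. It rests on reading the envelope sentence at face value.

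2. Hospital recruiting contradicts Study design on whether the 4-week run-in comes before randomisation, and Randomization and blinding does not resolve it. The weight of the text favours randomisation after the run-in. If Hospital recruiting were followed instead, run-in drop-outs would count as post-randomisation losses, in a sample with no stated allowance for them. The number affected is unknown.

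The sample size of 121 per group is not affected by how envelopes are issued.

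**What to change.** **Issue of envelopes.** Replace the patient's pick with sequentially numbered, sealed, opaque envelopes, opened strictly in order by the existing allocation administrator. Log the number, date and time at each opening, and reconcile the log with the computer list at close-out, accounting for every unused number. Recruitment has already begun according to Trial status, so apply this to the patients still to be randomised and record the date of the change.

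**Time point.** Reconcile Randomization and blinding and Hospital recruiting with Study design, so that randomisation happens once: after the run-in is complete, eligibility is confirmed, and the baseline VAS and RQLQ are recorded.

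**Cost.** Numbering the remaining envelopes, a short log, and edits to two sections. The administrator's role already exists, so no extra staff are needed. The sample size and the analysis do not change.
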